## Abstract

**Background:**

Health inequity is interlinked with the good health and well-being of an individual. Health inequity can be due to various socioeconomic factors like income levels or social status. Digital health interventions have the potential to reduce the existing health inequities.

**Objective:**

This study aims to identify determinants of social, economic, and health inequity in diverse settings to enhance healthy eating and active living. It further aims to design and develop a digital health intervention HEAL (Healthy Eating Active Living) that incorporates a human-centered design framework in order to improve healthy eating and active living among rural and urban population groups in Chennai, Tamil Nadu, India.

**Methods:**

A prospective, 3-year cohort study will be conducted. This study aims to recruit 6350 individuals across rural and urban settings of Chennai. A total of 11 sites have been selected for participation in the study. Data on sociodemographic characteristics; economic inequity; HEAL profile; depression, anxiety, and stress; well-being; sources of health information; perceived access to health care; health literacy; navigation of health literacy; and satisfaction with the health system will be gathered. This study would help to explore the determinants of social, economic, and health inequity across multiple sites. SAS (version 9.3; SAS Institute Inc) will be used for data analysis, and results will be reported as 95% CI and *P* values. This study’s findings will guide the design and development of a tailored, human-centered digital health intervention to enhance the health and well-being of Chennai’s population groups.

**Results:**

As of December 2024, the literature review for the development of the intervention has been completed. The recruitment for the baseline data collection will begin shortly, followed by the development of HEAL intervention.

**Conclusions:**

The proposed study will help in examining the role of the proposed HEAL intervention to enhance the health and well-being of the population groups of Chennai.

**International Registered Report Identifier (IRRID):**

PRR1-10.2196/41169

## Introduction

### Background and Rationale

The World Health Organization (WHO) identifies health inequities as “systematic differences in the health status of different population groups” [1]. Further, the WHO refers to health as “a state of complete physical, mental, and social well-being and not merely the absence of disease or infirmity” [2]. Consequently, research on health inequity is a central agenda component of the 2030 Sustainable Development Goals and various government and development dialogues [3,4]. Despite this, the WHO reports that health inequalities exist at varying degrees around the world, both within and between countries [5]. These inequalities further exacerbate health disparities between high-income and low-income, urban and rural, employed and unemployed populations, as well as between low-, middle-, and high-income countries [6] due to socioeconomic factors such as social status or income levels [7].

According to the Centers for Disease Control and Prevention, health equity can be attained when every individual can “attain his or her full health potential” and no one is “disadvantaged from achieving this potential because of social position or other socially determined circumstances” [8]. This also emphasizes the significance of measuring health inequity, promoting opportunities and monitoring the progress in health and intersectoral strategies. Additionally, measuring the interrelationship between health and its social determinants is vital to promoting effective interventions for health equity [9].

Inequalities are unfair, affect everyone, and are avoidable; however, the underlying factors causing inequality are imperfectly understood, and evidence on the effectiveness of interventions to reduce inequalities is limited [10]. Prior research has further highlighted the issue of good health for socioeconomically vulnerable groups and the need for targeted public health interventions in India [11]. A study indicated that health inequity in India is favored toward high-income populations and that despite services being available to people, there was a lack of awareness around it, especially in the rural region [12]. Considering the diversity in India and the prevalent social inequalities, the literature also emphasizes on the importance of research on health inequalities for monitoring health policies and programs [11].

Equity was also identified as one of the key principles of India’s 2017 National Health Policy [13]. However, with a limited evidence base of health equity in India, there is a need to generate empirical data for the variables that create, sustain, and reinforce inequity. This would further help the policy makers to prioritize and strategize the limited resources available for the health system of the country [14].

However, the paucity of data on health inequalities in India and the subsequent research gap on critical issues related to health inequity in the country also underscore the probable impact of policies and strategies deployed to enhance the well-being of population groups. Moreover, the COVID-19 pandemic has exacerbated the health inequity worldwide [15]. In addition, eating habits are possibly determined by the socioeconomic status of the individuals [16]. Thus, this study aims to enrich the current understanding of health inequity with empirical research. The findings will also help with the design and development of digital health intervention HEAL (Healthy Eating Active Living) to improve the good health and well-being of individuals by addressing social, economic, and health inequities. Tamil Nadu, India, was the chosen region of study as it seems to be a state that has progressed in health care in recent years, and hence, this study aims to see the receptivity to digital intervention of the study population in these settings [12].

### Study Objectives

This study aims (1) to identify determinants of social, economic, and health inequity to enhance healthy eating and active living among rural and urban population groups of Chennai, Tamil Nadu; (2) to design and develop a digital health intervention HEAL using the SMAART (Sustainable, Multi-Sector, Accessible, Affordable, Reimbursable, Tailored) model, targeted to enhance healthy eating and active living among rural and urban population groups of Chennai, Tamil Nadu; and (3) to evaluate impact of the proposed intervention to address burden of social, economic, and health inequity to enhance healthy eating and active living among rural and urban population groups of Chennai, Tamil Nadu.

## Methods

### Study Overview

The proposed research involves a multidisciplinary team with expertise in population health, epidemiology, sociobehavioral sciences, anthropology, and biochemical sciences.

### Study Design and Population

The HEAL cohort study is a prospective, 3-year cohort study with the aim to recruit 6350 individuals across rural and urban settings of Chennai, Tamil Nadu. The study sample will be recruited from Kannur; Pannur; Thirumenikuppam; Thodukadu; Kottaiyur; Nemili; Mannur; Kiloy; Ulundai; Narasamangalam; Karanai; Panimalar Medical College Hospital and Research Institute; Rural Training Health Centre Chennai; and Maligaipaddu village of Chennai, Tamil Nadu. Baseline evaluation will be performed at the time of recruitment of study participants. The study participants will be recruited through convenience sampling. This will serve as cross-sectional data to estimate the prevalence of determinants of social, economic, and health inequity.

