### Study Intervention

The HEAL intervention will be designed based on the SMAART model to enhance healthy eating and active living for the individuals participating in the study. This intervention will ensure the coordination of social, economic, and health-related parameters to enhance the health and well-being status of the population. The SMAART model works on the principles of data, information, and knowledge; human-centered approach; information processing theory; and humanistic, behavioral, and learning theories [17]. The intervention stage will have two parallel groups (case and control) for comparison. Individuals in the intervention group will be provided access to the informatics-based intervention for enhancing their healthy eating and active living. The participants from the intervention stage will be included in the study based on participants from the baseline stage consenting to participate in the intervention. The participants will be assigned to the intervention or control group through randomization. They would be provided information on good dietary habits and the importance of regular physical exercise for maintaining good health and well-being. Individuals in the control group will be provided an educational booklet as standard care. The intervention will be a tailored multilingual digital health intervention. Both the groups will undergo a series of baseline and follow-up assessments for estimation of change in eating patterns, physical activity, and well-being to assess the impact of intervention. The study location includes both the urban and rural areas of selected sites, and the study duration is 3 years. The study population includes all adults aged 18 years and older. The inclusion criteria are (1) individuals aged 18 years and older, (2) individuals from both urban and rural areas, and (3) individuals who consent to participate in the study.

Efforts will be made to include individuals of varied age groups, gender, location, and socioeconomic status. The exclusion criteria consist of (1) individuals younger than 18 years of age, (2) individuals who would not give their consent, and (3) individuals who have impaired cognition.

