### Limitations

This study’s limitations include that it is confined to one geographic region, and implementing it in diverse geographic and population settings would help to better understand and compare the impact of the HEAL intervention.

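### A convenience sample is given the task of estimating prevalence; the planned confidence intervals do not cover the selection error, and the Limitations do not mention it

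*Protocol article*

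**What the plan says.** Study Design and Population sets the recruitment target ("aim to recruit 6350 individuals across rural and urban settings of Chennai, Tamil Nadu"), lists the recruitment places, which are mostly villages but include a medical college hospital and a rural training health centre, and then states: "The study participants will be recruited through convenience sampling. This will serve as cross-sectional data to estimate the prevalence of determinants" of inequity. The first of these two sentences gives the sampling method and the second gives the purpose of the baseline data.

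The Study Objectives are framed for a population ("to enhance healthy eating and active living among rural and urban population groups of Chennai, Tamil Nadu"), and Study Intervention defines the study population as all adults from 18 years. The only step towards a balanced sample is also in Study Intervention: "Efforts will be made to include individuals of varied age groups, gender, location, and socioeconomic status".

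Data Analysis plans means, standard deviations and frequencies, with results reported at 95% confidence and P<.05. It describes no weighting or standardisation. The Limitations section names geography alone: "This study’s limitations include that it is confined to one geographic region".

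**The concern.** To estimate a prevalence, one needs a known chance of selection or a stated model for it. Convenience sampling supplies neither, and the article states no model. People who are easy to reach can differ in income, work, literacy and contact with care, and these are among the things measured at baseline. The two health facilities make this concrete. The baseline includes perceived access to health care, health literacy and satisfaction with the health system, and people met at a facility may already have reached care.

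At stake is what the baseline frequencies may be taken to mean. With 6350 people their intervals will look precise. A reader could take them as prevalences for rural and urban Chennai, and nothing in the Limitations warns against it. The article also expects baseline findings to show which areas an intervention should address.

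**Working it through.** **Is there a figure to reproduce?** No. The article gives the target of 6350 without an expected prevalence, a precision or a design effect. The check is therefore an illustration.

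**Inputs.** From the article: n = 6350 and 95% confidence. Assumed, because the article gives neither: true prevalence p = 0.30, and a selection ratio R, meaning how many times as likely a person with the characteristic is to be recruited as a person without it.

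**Step 1: sampling error.** The half-width under simple random sampling is 1.96 × √(p(1−p)/n) = 1.96 × √(0.30 × 0.70 / 6350) = 1.96 × 0.00575 = 0.0113, or 1.13 points. Clustering by place would widen a properly computed interval, but it would not remove a shift in the estimate.

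**Step 2: selection error.** The expected sample frequency is pR / (pR + 1 − p).

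| R | Calculation | Sample shows | Bias (points) |
|---|---|---|---|
| 0.8 | 0.240 / 0.940 | 25.5% | −4.5 |
| 1.05 | 0.315 / 1.015 | 31.0% | +1.0 |
| 1.25 | 0.375 / 1.075 | 34.9% | +4.9 |
| 1.5 | 0.450 / 1.150 | 39.1% | +9.1 |

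The sample size does not appear in this formula. A larger n narrows the interval in step 1 and leaves the bias in step 2 unchanged.

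**Step 3: where the two are equal.** The bias equals the half-width when the sample frequency is 0.3113, that is at R = (0.3113/0.6887) / (0.30/0.70) = 1.055.

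**Step 4: effect on coverage.** With bias b and standard error SE = 0.00575, the coverage of the nominal 95% interval is Φ(1.96 − b/SE) − Φ(−1.96 − b/SE). At p = 0.30 this is about 59% for a bias of 1 point, 6% for 2 points and 0.1% for 3 points. So a bias that still lies inside the half-width already costs coverage. How much is lost depends entirely on a bias that nobody knows.

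**The case against.** The strongest reply is that the plan claims less than it seems to. Prevalence is named as an aim of this study only once, in Study Design and Population, and that sentence names no target population. The first objective is to identify determinants, which Data Analysis assigns to multivariate regression, so it concerns associations. The 95% sentence covers all results and is not specific to prevalence. Convenience recruitment is openly stated, and a condensed article may leave details of the sampling frame and weighting to a fuller document.

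Much of this stands, and it rules out four stronger readings:

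- A reader might infer that the baseline figures have no population meaning at all. They do describe the recruited sample. They could extend further if selection were unrelated to the outcomes given measured covariates, but the article does not state that assumption.
- A reader might infer that the intervals will very probably miss the true value. That depends on the selection ratio. At 1.05 the bias is about 1.0 point, inside the 1.13-point half-width, and the article gives no information on the ratio.
- A reader might infer that the first objective fails. Convenience sampling can bias associations too, but the figures above concern a marginal frequency and do not measure that.
- A reader might infer that the trial stage is compromised. Allocation there is by randomisation among consenting baseline participants, so the comparison between groups is not invalidated by how they were recruited.

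The reply does not remove the two consecutive sentences that give a convenience sample a prevalence task. Both method and purpose are stated, so a fuller document would have to contradict the article to repair this. The promised effort at variety has no stated quotas or frame, and variety is not representativeness.

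**Conclusion.** The concern holds as a mismatch between the stated sampling method and the stated use of the baseline data, together with an undisclosed limitation. Confidence intervals computed as usual from these data would express sampling error only. Under an assumed prevalence of 30%, selection ratios of 1.05 to 1.5 would shift the estimate by about 1 to 9 points against a half-width of 1.13 points. These sizes are illustrative, and the actual direction and amount are unknown. The structural point, that bias from selection does not fall with n, needs none of the assumed values. It limits what the study may conclude from its baseline frequencies. It should be fixed, but it does not defeat the study.

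**What to change.** 1. In Study Design and Population, replace the prevalence aim with wording such as: *the baseline data will describe how often the determinants occur in the recruited sample and will be used to estimate their associations*.
2. State that neither the frequencies nor their intervals will be presented as population prevalences for Chennai.
3. Report the frequencies by recruitment source, village versus health facility.
4. Add selection by convenience sampling to the Limitations.

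Frequencies weighted to census margins may be shown as a sensitivity analysis. They correct only for the variables used in the weights: weighting on age, sex and urban or rural residence would leave selection on income, literacy or access to care largely in place. Weighting therefore cannot replace items 1 to 4.

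If a prevalence claim is wanted, it would need probability selection within the villages with matching weights, including a weight for the number of adults where one adult is drawn per household. The claim would be confined to those villages, since the two facilities have no household frame. That is an optional and costlier change. It needs household listing and call-backs, and the timeline allots months 2 to 5 to baseline data collection.

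Items 1 to 4 cost little: revised text, one extra tabulation and a weaker claim. The Results section says baseline recruitment has yet to begin, so they can be made in time.

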### Study Intervention

The HEAL intervention will be designed based on the SMAART model to enhance healthy eating and active living for the individuals participating in the study. This intervention will ensure the coordination of social, economic, and health-related parameters to enhance the health and well-being status of the population. The SMAART model works on the principles of data, information, and knowledge; human-centered approach; information processing theory; and humanistic, behavioral, and learning theories [17]. The intervention stage will have two parallel groups (case and control) for comparison. Individuals in the intervention group will be provided access to the informatics-based intervention for enhancing their healthy eating and active living. The participants from the intervention stage will be included in the study based on participants from the baseline stage consenting to participate in the intervention. The participants will be assigned to the intervention or control group through randomization. They would be provided information on good dietary habits and the importance of regular physical exercise for maintaining good health and well-being. Individuals in the control group will be provided an educational booklet as standard care. The intervention will be a tailored multilingual digital health intervention. Both the groups will undergo a series of baseline and follow-up assessments for estimation of change in eating patterns, physical activity, and well-being to assess the impact of intervention. The study location includes both the urban and rural areas of selected sites, and the study duration is 3 years. The study population includes all adults aged 18 years and older. The inclusion criteria are (1) individuals aged 18 years and older, (2) individuals from both urban and rural areas, and (3) individuals who consent to participate in the study.

Efforts will be made to include individuals of varied age groups, gender, location, and socioeconomic status. The exclusion criteria consist of (1) individuals younger than 18 years of age, (2) individuals who would not give their consent, and (3) individuals who have impaired cognition.

### Ethical Considerations

This study (protocol PMCHRI-IHEC-067) gained approval from the Panimalar Medical College Hospital and Research Institute Institutional Human Ethics Committee (Central Drugs Standard Control Organization Registration ECR/1399/Inst/TN/2020) in March 2022, with approval PMCH&RI/IHEC/2021/078 dated March 15, 2022. The study will be conducted according to the Declaration of Helsinki, as it involves human participants [18].

The institutional review board–approved informed consent form will be administered by the research team to the eligible individuals for the study. The research team will describe the study, time required, and benefits of the study results to the participants, and those willing to participate and give their consent will be enrolled in the study. Written informed consent will be obtained in both English and local Indian dialects at the time of data collection if the participants are able to read and understand the questionnaire. In the case of participants without formal education, an audio recording of the consent will be done. Study participants will be allowed to withdraw from the study at any time [19]. No compensation will be provided.

Data security will be ensured through regular backups in password-protected computers in the locked office of the principal investigator. Data will be stored for 5 years from the point of study completion, after which it will be destroyed. All the physical data files will be stored in a locked file cabinet in the office. The information will be accessible to members of the research team only.

### Data Collection, Data Entry, and Quality Assurance

Data collection and data entry will be performed by a team of trained field data collectors and data management. Data will be gathered in the field on paper and then entered on the computer. The data will be entered into the computer using Excel (Microsoft Corp). For quality assurance, a clearly defined data collection and management protocol will be in place. This will include a well-defined study manual with all the relevant instructions. For quality assurance, we will have a trained team of data collectors, weekly meetings with the research team, weekly data checks, maintenance of study participant contact, and maintenance of study participant data instrument logs.

### Variable Assessment

#### Sociodemographic Characteristics

Information will be collected on the participant’s age, gender, educational status, migration status, disability status, occupation, household size, family size, income, and number of earning members in the household.

#### Economic Inequity

The wealth index is a division of households into 5 wealth quintiles to show the relationship between wealth, population, and health indicators [20].

#### HEAL Profile

Data will be collected on the respondent’s health and lifestyle profile. We will use the WHO STEPwise approach to noncommunicable diseases risk factor surveillance questionnaire. It is a simple, standardized method for collecting, analyzing, and disseminating data on key noncommunicable disease risk factors in countries. The survey instrument covers key behavioral risk factors: tobacco use, alcohol use, physical inactivity, and unhealthy diet, as well as key biological risk factors: overweight and obesity, raised blood pressure, raised blood glucose, etc [21].

